Inmates who arrive on each intake night (Monday through Friday) will be assigned to be offered testing and approached for participation in the study at one of three time points based on the total number of inmates proceeding through intake that night and their arrival times to the jail. One third of inmates will be assigned to be approached for routine HIV testing and study participation the night of intake itself during routine health screening and mental health assessment (9pm – 1am). One third of inmates will be assigned to be approached for routine HIV testing and study participation the evening following intake when all arriving inmates undergo a routine physical exam. The final third of inmates will be assigned to be approached for routine HIV testing and study participation seven days after arriving at the facility. This last group will not have HIV testing conducted during any routine health procedures as with the first two groups. Even though there are no routine health procedures conducted at this time point, we are still interested in testing this group seven days after intake because many in this testing group would have received seven days of medications and have completed a detox protocol if necessary. We therefore believe that a higher proportion of individuals in this last testing group will be more stable and be competent to consent to testing compared to the prior testing groups, although many of them might have bonded out or been released from the facility by this point. Although this time point is of less interest than the first two time points, because this is a pilot study, we believe that the data we collect from testing at this time point would provide us with valuable information that could better inform our research design for conducting a larger testing study in the future.

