3.A.2 Description of Study Sites: We will conduct our study at two jail sites: New Haven Community Correctional Center (men) and the York Correctional Institution (women) located in Niantic. There are on average 25 unique intakes at NHCCC and 20 at York each evening. Services available at both facilities include: a general medical clinic, HIV consultation services, voluntary HIV testing, detox and treatment for those with opioid dependence, standardized detox procedures for alcohol and benzodiazepine withdrawal, an inpatient medical infirmary, a mental health assessment unit, substance abuse counseling, and a variety of support groups. York provides its inmates with methadone treatment for opioid dependence. All inmates undergo a standard, half-day orientation session by a correctional officer the morning after admission to the facility; a health services staff member also provides an overview of services available, including access to voluntary HIV testing. Voluntary HIV testing is available at both sites and can be accessed through inmate request or referral from a clinic based on identified risks or the presence of symptoms associated with HIV. New entrants to the facilities undergo routine medical and psychiatric assessment each weekday evening during the second (3pm-11pm) or third (11pm–7am) shift as part of intake, depending on when they arrive, and are treated according to evidence-based protocols for management of acute intoxication, withdrawal or serious mental illness.

3.A.3 Inclusion/Exclusion Criteria: All newly incarcerated inmates will be eligible.

3.A.4 Sample Size Determination

As stated previously, our primary outcome is the percentage of subjects who consent to and receive an HIV test at a given time-point at each jail, with this primary outcome being assessed independently for each the male and the female jail. The sample size calculations for each jail are exactly the same, even though programmatically relevant and likely observed results and effect sizes are different for each jail. Namely, women are expected to exhibit higher uptake rates.

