For both jails, sample size calculations are made comparing the uptake at intake compared to subsequent timepoints. While, for the purposes of this pilot study, we do have three arms to have a more complete programmatic experience, the most relevant analysis is to just compare intake with post-intake. Since we are randomizing 1:1:1, this results in a 2:1 comparison for the primary outcome comparing the intake group with the collapsed post-intake groups. Table 1 provides sample size estimates for each arm, based on using the chi-square tests to compare the proportion uptake at each time-point within each jail setting and calculated using the standard sample size formula:

Where p is the proportion who receive an HIV test at intake, alpha is the type 1 error rate, beta is the type 2 error rate, and delta is the difference between the intake and post-intake groups. Plausible ranges of uptake rates are garnered from our current experiences in the jail system, through extensive clinical interviews and discussions with jail counselors. Only one other study has assessed routine testing in a jail setting. That study, however, is likely to have significantly higher uptake rates than will be seen in our study, since many of the subjects were repeat testers and the program had been running in that jail for some time.23

At our best-estimated initial uptake of 60% for men and 75% for women, 100 subjects in each arm will detect differences of 16% and 13%, respectively, with a type 1 error rate of 0.05 and power of 80%.

| **Table 1. Sample Size Calculations** | | |  |  |
| --- | --- | --- | --- | --- |
| **Jail Setting** | **Intake** | **Subsequent Time-points** | **N (each arm)** | **3N (Total Subjects)** |
| Men | 50% | 65% | 126 | 378 |
| 55% | 70% | 121 | 363 |
| **60%** | **76%** | **98** | **294** |
| 65% | 80% | 101 | 303 |
| 70% | 84% | 103 | 309 |
| Women | 65% | 80% | 101 | 303 |
| 70% | 84% | 103 | 309 |
| **75%** | **88%** | **100** | **300** |
| 80% | 92% | 93 | 279 |
| 85% | 95% | 99 | 297 |

3.A.5 Procedures

3.A.5.1 Testing

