Inmates who arrive on each intake night (Monday through Friday) will be assigned to one of three testing groups based on the total number of inmates proceeding through intake that night and their arrival times to the jail. One third of inmates will be assigned to be approached for routine HIV testing and study participation the night of intake itself during routine health screening and mental health assessment (9pm – 1am). One third of inmates will be assigned to be approached for routine HIV testing and study participation the evening following intake when all arriving inmates undergo a routine physical exam. The final third of inmates will be assigned to be approached for routine HIV testing and study participation seven days after arriving at the facility. These procedures have been described above in the previous section.

1. **Inclusion/Exclusion Criteria:** What are the criteria for subject inclusion or exclusion? How will eligibility be determined, and by whom?

All newly incarcerated inmates will be eligible to be approached for testing and inclusion in this study. Individuals who are suicidal or incompetent to consent will be excluded from the study. We will keep track of how many people are incompetent to consent, but we will not keep data on those individuals or carry out the testing. The standardized MacArthur Competence Assessment, as well as the clinical judgment of the DOC clinicians who put individuals on suicide watch or psychiatric holds will be used to determine whether or not someone is eligible to participate.

1. **Subject Population:** Provide a detailed description of the proposed involvement of human subjects. Describe the characteristics of the subject population, including their anticipated number, age range and health status.

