- the case manager completes the necessary paperwork for the inmate to participate in the AIDS Drug Assistance Program upon release, which provides free antiretroviral medication once the inmate is in the community.  Inmates are also strongly advised to apply for reinstatement of SAGA (State-Administered General Assistance), administered by the Connecticut State Dept of Social Services, as well as for Title 19 which provides Medicaid.
- the case manager schedules an appointment for the inmate to meet with an HIV provider in geographical proximity to the inmate’s local community.

1. **Data and Safety Monitoring Plan:** Please include a Data and Safety Monitoring Plan (DSMP) that includes an explicit statement of overall risks, addresses attribution and grading of adverse events and describes procedures for monitoring the ongoing progress of the research and reporting adverse events. For more information, please see the HIC website: <http://info.med.yale.edu/hic/forms/index.html>

Because we are not proposing a clinical trial, it is not appropriate to have a Data and Safety Monitoring Board (DSMB). However it is essential to have a Data and Safety Monitoring Plan (DSMP). We are proposing conducting a prospective observational study to evaluate acceptability of routine testing HIV and a prospective routine HIV testing study in the jail setting. The PI and research staff will review any reports of adverse events related to the study. Serious, unanticipated adverse events will be reported within 48 hours to the HIC, and funding agencies. There are no anticipated serious adverse effects. However, listed below are a number of items that could potentially be adverse events for participation in this study:

- 1. Breaches of confidentiality: Participants will be notified that they should let study staff or the HIV testing counselor know if there are any breaches in confidentiality. If a breach were reported, this would then be reported immediately to the rest of the study team and principal investigator. An initial investigation would be undertaken and simultaneously reported to the HIC using standard university procedures.

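### The sample size section claims 1:1:1 randomization, but the stated assignment rule uses nightly head count and arrival time, so the primary comparison is not protected against confounding by arrival time

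*Protocol*

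**What the plan says.** Protocol section 3.A.4 (Sample Size Determination) justifies the primary comparison with "Since we are randomizing 1:1:1, this results in a 2:1 comparison for the primary outcome", setting the intake group against the two later groups combined.

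Section 3.A.1 (Overview) gives the operating rule. One third of each night's arrivals go to each time point, "based on the total number of inmates proceeding through intake that night and their arrival times to the jail". Section 3.A.5.1 (Testing) repeats it. Section VI (Recruitment Procedures) and Section VII (Process of Consent) say the same in nearly the same words: inmates "will be assigned to one of three testing groups based on the total number of inmates proceeding through intake that night and their arrival times". None of the four mentions a random sequence, a chance element or concealment.

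The Data and Safety Monitoring Plan in Section VIII says that no clinical trial is proposed and describes the work with "We are proposing conducting a prospective observational study". The same sentence goes on to name a prospective routine testing study as well.

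For analysis, 3.A.4 refers to chi-square tests. Section 3.A.7 (Analytic Plan) names Mantel-Haenszel tests without a stratification factor. It lists covariates for a logistic model, and arrival time and intake night are not among them.

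**The concern.** Randomization is what allows a difference in uptake between intake and later time points to be read as an effect of timing, and it is what supports the 5% error rate of the test. A rule built on arrival order does not supply it. If inmates who arrive at different points in the evening differ in their underlying chance of being competent, consenting or still being in the jail, that difference enters the comparison along with timing.

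Two uses of the result depend on this. Section 3.A.1 says the primary outcome is assessed separately for each jail because policy is made separately for men and women. Section 3.A.7 says the data will supply the effect size for a larger randomized trial. Any bias in the pilot would be carried into both. Allocation also cannot be repaired after enrolment, and as written staff cannot tell which rule to apply.

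**Working it through.** **1. The statements side by side.**

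| Place in protocol | How arms are formed |
|---|---|
| 3.A.4 | Randomized 1:1:1 |
| 3.A.1, 3.A.5.1, Section VI, Section VII | Nightly count and arrival times |
| Section VIII, monitoring plan | Not a clinical trial; an observational study and a routine testing study |

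The first two rows cannot both describe the procedure unless a random step exists that the text omits.

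**2. The plan's own sample size.** Inputs from 3.A.4: men 60% v 76%, women 75% v 88%, type 1 error 0.05, power 80%, allocation 1 (intake) to 2 (later). The protocol does not state whether the test is one- or two-sided; two-sided reproduces its figures. With p̄ = (p1 + 2·p2)/3 and δ = p2 − p1,

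n = [1.960·√(1.5·p̄(1−p̄)) + 0.842·√(p1(1−p1) + p2(1−p2)/2)]² / δ²

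- Men: p̄ = 0.7067; n = (1.0929 + 0.4844)² / 0.16² = 97.2, rounded up to 98. Table 1 gives 98.
- Women: p̄ = 0.8367; n = (0.8874 + 0.4126)² / 0.13² = 99.99, rounded up to 100. Table 1 gives 100.

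The other rows of Table 1 also reproduce. At 100 per arm the power is 81% (men) and 80% (women). The arithmetic is sound; the fault lies in the allocation.

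**3. What an imbalance would do (illustration).** Suppose timing has no effect, but the arms differ by b in underlying uptake because of who arrives when. The documents give no value for b; 3 to 10 points is an assumed range. With p2 = p + b, 100 intake and 200 later inmates,

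SE0 = √(p̄(1−p̄)(1/100 + 1/200)), SE1 = √(p(1−p)/100 + p2(1−p2)/200),

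P(reject) = Φ((b − 1.96·SE0)/SE1) + Φ((−b − 1.96·SE0)/SE1).

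- Men, 60% v 65%: SE0 = 0.0590, SE1 = 0.0595; Φ(−1.104) + Φ(−2.786) = 0.135 + 0.003 = 0.137.
- Women, 75% v 80%: SE0 = 0.0505, SE1 = 0.0517; Φ(−0.945) + Φ(−2.879) = 0.172 + 0.002 = 0.174.

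| Assumed imbalance b | Men (base 60%) | Women (base 75%) |
|---|---|---|
| 0 | 5% | 5% |
| 3 points | 8% | 9% |
| 5 points | 14% | 17% |
| 8 points | 28% | 38% |
| 10 points | 41% | 56% |

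An imbalance in the other direction hides a real effect. If 5 points are lost from the planned differences, power falls to about 48% (men, 60% v 71%) and 38% (women, 75% v 83%).

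**4. How much imbalance the rule could create.** This depends on what is done each night, which the text does not say. Giving consecutive thirds of the evening to the three groups would make arm and arrival time almost the same variable. Rotating every third arrival would leave little separation, though it would still be neither random nor concealed. Because thirds are taken within each night, differences between nights, such as weekend arrests that arrive on Monday, should roughly balance. The exposure is to arrival order within a night.

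**The case against.** The strongest reply is that the protocol shows a wording conflict, not a biased comparison. Much of this stands.

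- A reader might infer that the arms do differ systematically and that the comparison is confounded. The documents do not support that. The exact rule is not stated, and nothing links arrival time within a night to competence, consent, charge, intoxication or release.
- A reader might also infer that late arrivals can only fall in the later groups, because the Day 0 window closes at 1am (3.A.1) while intake assessment takes place "during the second (3pm-11pm) or third (11pm–7am) shift as part of intake, depending on when they arrive". The latter gives staff shifts, not an end time for intake, and the 1am window already spans both shifts. Section 3.A.5.2 says intake goes on very late but gives no hour. Nothing says that inmates are processed after the window closes.
- The observational label is weak evidence about allocation, since its sentence also names a routine testing study.
- Predictable assignment does less harm than usual here: every new inmate may be approached, and assignment comes before approach and consent.
- This is a pilot, and covariate adjustment is often left to an analysis plan.

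These points limit the claim without removing it. The protocol states its rule four times, and the rule as stated has no random element. It also powers a formal 5%, 80% comparison on the strength of randomization. If a random list applied in log order is what was meant, the text does not say so.

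**Conclusion.** The protocol claims a property that its stated assignment rule lacks, and no analysis it describes compensates. The supportable conclusion is that the primary comparison is not protected against confounding by arrival time within the night. Whether bias would occur, in which direction and how large cannot be determined from the document. The error rates of about 14% (men) and 17% (women) rest on an assumed 5-point imbalance, a normal approximation, 100 v 200 inmates and no true timing effect; they show sensitivity and are not a forecast. The planned sample size is unaffected. The matter should be settled before the first inmate is assigned.

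**What to change.** 1. In 3.A.1, 3.A.5.1, Section VI and Section VII, replace the arrival-time rule with a pre-generated random list for each jail, in permuted blocks of varying size (for example 3 and 6), concealed until the inmate is logged. Apply it to each logged inmate before any approach, and analyse all inmates as assigned. With about 25 and 20 intakes an evening (3.A.2), small blocks keep the nightly thirds nearly intact.
2. Reconcile the Day 0 window, which ends at 1am in 3.A.1 and at 2am in the 3.A.6 figure. State how inmates who cannot be reached within it are handled. They need not be excluded; 3.A.3 makes all new inmates eligible.
3. If randomization is not feasible, delete the word randomizing from 3.A.4, state the exact rule, adjust the primary comparison for arrival time and intake night, and describe it as non-randomized. This is the weaker option: adjustment removes only what it measures, and it cannot help if some arrival times lead to only one arm.
4. Make the design wording in the Section VIII monitoring plan agree with the choice.

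The cost is a printed list or numbered envelopes for each jail, a logging step at intake, and edits to the protocol text. The number required stays at about 100 per arm.

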Table 1: Schedule of Interviews

| **Interview Instrument** | **Administered to Inmate** | **Administered to Staff** |
| --- | --- | --- |
| MacArthur Competence Assessment to evaluate medical ability to consent to testing | X |  |
| Demographics | X |  |
| History of previous HIV testing experiences | X |  |
| Court dates | X |  |
| Likelihood of remaining incarcerated | X |  |
| Willingness to HIV test now if it were made available | X |  |
| Attitudes about HIV testing in jails and prisons | X |  |
| Clinical Opiate Withdrawal Scale (COWS) | X |  |
| Clinical Institute Withdrawal Assessment of Alcohol (CIWA) | X |  |
| National Center for Health Statistics (NCHS) K6 Scale for Serious Psychological Distress | X |  |
| Staff attitudes about routine HIV testing in jails |  | X |

3.A.5.2 Delivery of HIV Test Results

1. Timing of delivery of test results will differ depending on the testing group. For the Day 1 and Day 7 testing groups, delivery of test results will be given the same evening that testing occurs. For the Day 0 testing group, however, delivery of test results will be given the following morning instead of the night of intake. Although this protocol is to determine the feasibility of future implementation of a rapid routine HIV testing program, for the purposes of this study it is not logistically possible for us to deliver preliminary positive test results the night of intake. This is because delivery of preliminary positive test results must be done by the DOC HIV counselors. Because intake procedures only start around 9pm and continue very late into the night, it is not logistically possible for us to hire the DOC HIV testing counselors to work during those hours, as they must work the first shift (7am-3pm). Therefore, after extensive consultation with jail HIV testing counselors, nursing and medical staff, and [name], the HIV Prevention Program Manager for the Department of Corrections, we have decided to have delivery of all test results for the Day 0 testing group delivered early the following morning starting at 6:30AM. The counselors have agreed to be on call to come back during the 2nd shift (3pm-11pm) to deliver positive results to inmates tested on Days 1 and 7. For each facility, we have made these arrangements with HIV counselors who live in close geographic proximity to each jail.

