2. Delivery of all preliminary positive results will be given by HIV testing counselors working at both correctional facilities. Delivery of all negative results, however, will be delivered by research study staff. One of our main reasons for choosing this method is because we want to ensure that subjects diagnosed as preliminarily positive have sufficient time to meet with counselors for post-test counseling. Also, if counselors must meet with inmates to deliver both positive and negative results, they may not have enough time to deliver all results prior to new inmates needing to return to court or bonding out. This would mean that some individuals in the Day 0 testing group could bond out or be taken to court in the morning before receiving test results. The bondsman arrives at 8am at both facilities – therefore, in order to ensure that all subjects receive their test results before meeting with the bondsman, both positive and negative test results will be delivered early the following morning starting at 6:30AM.
3. Although delivery of negative test results by research study staff is not the current standard of care at both study sites, it does simulate the standard of care that would be delivered if routine HIV testing were to be adopted. According to the revised CDC guidelines for routine testing, “HIV-negative results may be conveyed without direct personal contact between the patient and the health-care provider.” Only HIV positive results should be communicated confidentially through personal contact by a clinician, nurse, mid-level practitioner, counselor, or other skilled staff. Furthermore, prevention counseling should not be required as a part of HIV screening programs in health-care settings. 2 This protocol of delivery of negative test results by research study staff has also been reviewed and preliminarily approved by the Department of Corrections Research Committee, pending a signature from the Deputy Commissioner. The DOC Research Committee must give final approval to any study proposed to be conducted in the Connecticut Department of Corrections.

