4. The research staff working on this study have considerable collective experience with HIV testing, counseling, as well as interacting with inmates and providing healthcare to the incarcerated. One member of the study staff has been a prison nurse with the Department of Corrections for over twenty years, and has been involved with providing intake health assessments at York C.I. for over ten years. Another member of the team is a Connecticut Department of Public Health certified HIV counselor and has many years of experience conducting rapid HIV testing and counseling. All members of this team have had experience conducting rapid HIV testing and delivering negative test results.
5. Although we are using rapid HIV tests for this study, we will inform the inmates approached for the study that test results can be received “within a short period of time”, rather than specifying that results can be received in as little as 20 minutes. The reason we have chosen to do this is because we do not want to create an expectation that if the inmate chooses to be tested, s/he will receive results in 20 minutes. As we stated above, although this study aims to simulate future implementation of a routine rapid HIV testing protocol, there are operational and logistic challenges to delivering all results in twenty minutes both for this study and in true clinical practice. If, for instance, there is a preliminary positive test result in the Day 0 testing group, we will have to wait until the morning in order for the counselor to deliver the result. For the Day 1 and Day 7 testing groups, we will have to call the HIV counselor to come in to deliver a preliminary positive test result, which will likely take more than twenty minutes. We do not want to create additional anxiety for the inmates by exposing them to a longer than expected waiting period for results. If routine testing were actually implemented in this setting, there are a number of factors, such as a medical or behavioral emergency with another inmate that could preclude delivery of test results within twenty minutes.

3.A.6 Study Design (see figure below)

INMATES ARRIVE AT YORK C.I. OR NEW HAVEN C.C.C. FOR INTAKE PROCEDURES

**DAY 0:** 1/3 TESTED ON INTAKE NIGHT DURING HEALTH ASSSESSMENT

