## Section VIII: Protection of Research Subjects

1. **Risks:** What are the reasonably foreseeable risks, discomforts, or inconveniences associated with participation in the research?

The risks in this study are minimal – potential risks could however include breaches of confidentiality within the jail. If jail guards or other inmates were to learn of an individual’s HIV status, it could lead to discriminatory behavior and even physical harm. In addition, learning of one’s own HIV status could be both upsetting news and potentially difficult information for inmates to deal with constructively, especially within the often chaotic correctional setting. Lastly, it is possible that with the high turnover in the jail setting, an inmate might test preliminarily positive using the OraQuick rapid HIV test but will be released before a confirmatory result can be delivered.

The published sensitivity and specificity for the OraQuick Advance Rapid HIV-1/2 Antibody oral test are 99.3% (95% confidence interval [CI] = 98.4% -- 99.7%) and 99.8% (CI = 99.6% -- 99.9%). According to these reported rates, it would be expected that for every 1000 individuals tested, 2 would receive false positive results.

Our research protocol proposes to test 600 individuals. Therefore, while it is still possible for one of our subjects to falsely test positive, the likelihood is very small.

Please note: Potential research risks include more than physical harm; risks may also include, for example, emotional or psychological harm, risk of social stigmatization, economic or legal risk.

1. **Minimizing Risks:** How will the above-mentioned risks be minimized?

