Potential instances for breaches of confidentiality include during the interview process or during delivery of positive test results. From our research efforts and provision of clinical care for inmates within the correctional system, we have paid careful attention to potential breaches of confidentiality for subjects undergoing interviews. [name], the Principal Investigator, has written extensively on the legal and ethical issues with regard to conducting clinical trials among prisoners.30,31 All interviews will be conducted individually during the second shift when rooms are more accessible for consent procedures and privacy can be ensured. Rooms are private and the information collected from individual interviews will be confidential. Appointments will be staggered to avoid participant encounters in the interview room or in the outside hallway. All information will be stored in password-protected computers with double-password protection for opening specified files. All confidential information (study instruments, HIV status, etc.) will be recorded with study participant number only and maintained in locked cabinets within our offices at the Yale University AIDS Program and will only be available to be opened by the Study Coordinator, study staff, or the Principal Investigator. Electronic databases will be maintained through password-protected computers and files and maintained on a single computer at the Yale University AIDS Program. No data will be stored on laptops, flash drives, or be transported via email or any other medium. The data will be stored according to a study ID number and therefore will contain no names, prison ID numbers, or any other personal identifiers. Identifying information will not be stored. All data will be encrypted using encryption software provided by Yale Information and Technology Services.

Study participants should not have to worry about being identified as HIV+ by participating in the study, since all newly entering inmates will be eligible, most of whom will not be HIV+. We have designed this study so that capacity is not so excessive that confidentiality is likely to be breached.

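### The rule on who delivers each HIV result, and when a counselor is called in, lets an observer infer a preliminary positive, and no stated safeguard masks this

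*Protocol*

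**What the plan says.** Section IV, 3.A.5.2, item 2 splits delivery by result: "Delivery of all preliminary positive results will be given by HIV testing counselors working at both correctional facilities". The next sentence covers everyone else: "Delivery of all negative results, however, will be delivered by research study staff".

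Timing also follows the result. For Day 1 and Day 7, item 1 puts counselors on call for the second shift to give positive results. Item 5 says that "we will have to call the HIV counselor to come in to deliver a preliminary positive test result", and expects this to take more than twenty minutes. For Day 0, both kinds of result are given from 6:30AM the next morning, by the two different messengers.

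Section VIII, Risks, says of guards or other inmates learning someone's HIV status that "it could lead to discriminatory behavior and even physical harm". Minimizing Risks acknowledges where this may happen: "Potential instances for breaches of confidentiality include during the interview process or during delivery of positive test results". It also gives an assurance: "Study participants should not have to worry about being identified as HIV+ by participating in the study, since all newly entering inmates will be eligible".

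The other protections are individual private rooms and staggered appointments for interviews, coded data, use of existing medical facilities under DOC confidentiality rules for positive results, and individual attendance in private space (Confidentiality).

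**The concern.** The messenger is a marker of the rapid-test result. Under the rule, a tested inmate seen by a counselor for a result is preliminary positive, and one told by research staff is negative. On Day 1 and Day 7 evenings the counselor's arrival and the longer wait are a second signal.

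Closed doors keep the words private. They do not conceal which person an inmate is called to see, or that a counselor has come in out of hours. At stake is the harm that the protocol itself names, for subjects who are prisoners. The signal also precedes confirmatory testing, so an inmate with a false positive could be taken for HIV-positive.

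**Working it through.** The rule is procedural and the protocol gives no figure to reproduce. The arithmetic below only sizes the exposure.

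**Inputs.** HIV positivity about 2% (Section VIII, Minimizing Risks). Sensitivity 99.3%, specificity 99.8% and 600 tests (Section VIII, Risks). Intakes of 25 per evening at New Haven and 20 at York (3.A.2), one third per group. Uptake of 60% at intake and 76% afterwards for men, 75% and 88% for women (3.A.4, bold rows of Table 1). 100 per arm per jail.

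**Chance of a preliminary positive per test.** 0.02 × 0.993 + 0.98 × 0.002 = 0.01986 + 0.00196 = 0.02182.

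**Number of preliminary positives.**
- All 600 tested: 600 × 0.02182 = 13.1, of which 600 × 0.00196 = 1.2 are false.
- Table 1 uptake: men 60 + 76 + 76 = 212, women 75 + 88 + 88 = 251, total 463 tests. Then 463 × 0.02182 = 10.1, of which 463 × 0.00196 = 0.9 are false.

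**What the messenger reveals to someone who knows the rule.** Given a counselor, the probability of HIV is 0.01986 / 0.02182 = 91%, against 2% beforehand. Given research staff, it is 0.02 × 0.007 / (0.02 × 0.007 + 0.98 × 0.998) = 0.01%. If positivity were 1% or 4% (assumed values), the 91% becomes 83% or 95%.

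**How often a group contains a positive**, as 1 − (1 − 0.02182)^n:
- Day 0 at Table 1 uptake: n = 25/3 × 0.60 = 5 and n = 20/3 × 0.75 = 5, giving 10% at each jail.
- Day 1 or Day 7 at Table 1 uptake: n = 25/3 × 0.76 = 6.3 and n = 20/3 × 0.88 = 5.9, giving 13% and 12%.
- Upper limit with everyone assigned tested: n = 8.33 and 6.67, giving 17% and 14%.

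A group with a positive usually has only one. For n = 5, exactly one given at least one is 5 × 0.02182 × 0.97818^4 / 0.104 = 96%.

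**Safeguards against signals.** Eligibility of all entrants hides nothing at delivery, where subjects are separated by result. Private rooms and staggered appointments are described for interviews. Existing medical facilities, DOC rules and individual private space do cover delivery, but they protect what is said and recorded. None conceals who delivers or when.

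**The case against.** The split is deliberate. Item 2 wants enough counselor time for post-test counseling, and all results given before court or the bondsman's 8am arrival. Item 3 adds that it simulates routine testing and has preliminary DOC Research Committee approval. These reasons stand, and they justify who delivers. They do not bear on whether the split is visible.

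A reader might infer four stronger things that the documents do not support:
- That the protocol contradicts itself. The assurance "Study participants should not have to worry about being identified as HIV+ by participating in the study" concerns taking part, and the same answer admits delivery as a breach point. This is an unaddressed risk and no contradiction.
- That delivery has no protection. Minimizing Risks and Confidentiality give it some, and the Data and Safety Monitoring Plan provides for breach reporting.
- That every preliminary positive will be exposed. An observer must see who delivers and know the pattern. Nothing says that delivery is observed.
- That uptake will fall as inmates learn the pattern. No passage supports this.

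Counselors also handle voluntary testing and work 7am to 3pm, so contact with one is not specific in general. The signal is clearest on the on-call evenings and weaker in the morning, when delivery from 6:30AM runs into their normal shift.

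An ambitious remedy would also do harm. One room with equal visit lengths between 6:30 and 8:00 leaves 90 / 8.33 = 11 minutes each for a full Day 0 group at New Haven, which works against item 2's own reasons.

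**Conclusion.** The point holds as a gap in protection. Messenger and timing track the rapid-test result, an informed observer can infer it, and the stated measures do not mask it, although the protocol names both the harm and delivery as a breach point.

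About 10 to 13 subjects would be open to this inference, about 1 of them a false positive. The counts rest on the protocol's 2% positivity and test accuracy. The lower count assumes Table 1 uptake, and the upper assumes that all 600 are tested. How many would actually be identified cannot be derived from the protocol. The primary analysis is not shown to be affected. The case for a change is subject safety, at small cost.

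**What to change.** Keep who delivers which result. State in 3.A.5.2, and in Section VIII, Minimizing Risks, as the safeguard for delivery:
- All tested inmates are called from one list, in study-number order, to the same private medical area whatever their result. Which messenger they see is determined only inside it.
- On Day 1 and Day 7 evenings with a preliminary positive, results not yet given are delivered in list order once the counselor has arrived, still on the same evening.

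Do not require a single room or equal visit lengths, so that post-test counseling time and delivery before 8am are preserved. In Minimizing Risks, make clear that the existing assurance covers participation only.

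The cost is protocol wording and call-out logistics, with no added staff. Some negatives wait longer when a Day 1 or Day 7 group has a positive (about 12% to 13% of such groups at Table 1 uptake). Item 5 wants to avoid long waits, but results still come within the afternoon or evening that inmates are told to expect. The masking is partial: a held list hints that someone in the group is positive, and later confirmatory testing still sets that person apart.
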